#### CAM assessments

The CAM is an operationalised approach to applying the DSM delirium criteria. It has been used extensively in research and, to a lesser extent, in routine care. Administration takes 5–10 min. The CAM is positive, and delirium present, if there is sudden onset and a fluctuating course of inattention and either disorganised thinking or an altered conscious level.^11^ A structured approach to the identification of inattention and disorganised thinking will be adopted as described by O'Regan *et al*.^16^ Inattention will be assessed formally through the ‘Months of the Year Backwards’ (MOTYB) test.^16^ Disorganised thinking will be assessed using the methods outlined in the CAM administration manual.^11^ In addition, questions aimed at testing abstract reasoning (eg, explaining the meaning of a common proverb) will be used.^16^ Scoring of the CAM is described in detail in the CAM handbook;^11^ the CAM-severity scoring system will be adopted to allow the severity of delirium to be graded.^12^ The CAM assessments will be entered electronically into encrypted laptop computers.

#### DOSS assessments

The DOSS identifies specific features of affect or behaviour to facilitate recognition of DSM defined criteria for delirium. The DOSS is based on non-technical observations from nurses or carers as they attend to patients during routine care. Only minimal training is required for administration. This study will examine the 25-item DOSS rather than the 13-item scale (which is more weighted towards hyperactive delirium). The hypoactive delirium subtype has been shown to be twice as common as hyperactive delirium in the postacute setting^17^ and is associated with poor outcomes.^18^ However, hypoactive delirium is poorly detected, particularly by nursing staff.^19^ Methods to improve the detection of hypoactive delirium by nursing staff in the care home setting are therefore desirable. The full 25-item DOSS can be completed in 5 min.^20^ The 25-item DOSS has been shown to have content validity and internal consistency (Cronbach's α 0.93 and 0.96, respectively).^7^ Concurrent validities against international standard delirium diagnostic and severity instruments (the CAM and the Delirium Rating Scale—Revised—98)^7^
^10^ are good. In order to ensure that the 25-item DOSS is relevant to the UK care home environment, it has been necessary to reword some items (eg, to remove reference to interventions that would not be expected in the care home environment, eg, intravenous lines).

When the 13-item DOSS was derived from the 25-item DOSS, the original Likert scoring scale was dichotomised for each item to simply record whether a particular behaviour has, or has not, been observed during the course of a shift.^21^ For this study, each item of the 25-item DOSS will be scored 0 or 1 with a higher score indicating behaviour more in keeping with delirium (some items are reverse scored).

### Sample size calculation

Measurement of sensitivity of the DOSS requires identification of cases where CAM and DOSS are positive. Sample size calculation is therefore based on the number of positive delirium episodes (identified with the researcher-administered CAM) required to measure the sensitivity of the DOSS with 95% confidence that the observed value is within 95% of the true value. Using the pooled estimate for sensitivity (92%) of the DOSS from previous studies,^9^ and the normal approximation to the binomial proportion distribution, there would need to be 113 measurements of CAM positive delirium during the study period.

The study involves repeated assessments; there is therefore likely to be correlation between serial CAM measurements. An episode of delirium lasts, on average, 11 days in the long-term care setting.^22^ CAM measurements are 4 days apart. It is likely that there will be at least two CAM measurements during each episode of delirium. We have therefore assumed at least moderate correlation between CAM measurements (intraclass correlation coefficient of 0.5). Applying an inflation factor (of 1.5) to account for the study design effect due to the repeated measures would require 170 CAM positive measurements over the 9-month study period. A recent study of delirium in Canadian long-term care settings offers the best available estimate of delirium incidence in care homes of 21.8% in 24 weeks.^1^ We estimate that 170 CAM positive readings would be made in 258 residents over 36 weeks.

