## Methods and analysis

The DOSS study is a prospective observational cohort study, performed in UK long-term care settings over 24 months (May 2014 to May 2016). The 25-item DOSS, performed once daily by care home staff, will be measured against the temporally closest CAM (a research standard) performed two times per week by research staff for all participants. Feasibility of routine daily administration of the DOSS will be investigated by examining patterns and rates of missing data on care home staff completed DOSS assessments. To determine the diagnostic test accuracy of the DOSS, sensitivity, specificity, positive and negative predictive values and likelihood ratios of the DOSS for the detection of delirium will be calculated. The CAM has been validated as a measure of delirium severity^12^ and this will allow for a further investigation to determine whether the DOSS may also be used as a measure of delirium severity. Repeated daily DOSS measurements will be used to examine the scaling properties of the 25-item DOSS instrument. Item response theory will be used to determine whether the questions are measuring the same underlying constructs (delirium) and whether there are any redundant questions which may be removed to create a shorter, care home-specific DOSS.^13^

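### The target of 170 CAM-positive readings assumes two readings per episode, but the plan's own figures give 2.75 or more, so ±5 points needs about 212 readings

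*Protocol article*

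**What the plan says.** All the figures are in the Sample size calculation section of the protocol article. The target is the number of CAM-positive measurements needed to estimate DOSS sensitivity "with 95% confidence that the observed value is within 95% of the true value". The assumed value is 92%, and the result is that "there would need to be 113 measurements of CAM positive delirium during the study period".

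The section then allows for correlation between serial readings. It states that "An episode of delirium lasts, on average, 11 days in the long-term care setting" and that "CAM measurements are 4 days apart", and concludes: "It is likely that there will be at least two CAM measurements during each episode of delirium". It assumes an intraclass correlation of 0.5, applies an inflation factor of 1.5 and arrives at 170 readings. Using an incidence of 21.8% in 24 weeks, it ends: "We estimate that 170 CAM positive readings would be made in 258 residents over 36 weeks".

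The Study assessments section schedules the CAM twice a week for nine months. It pairs each CAM with the DOSS nearest to it in time.

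**The concern.** A design effect for repeated readings depends on how many readings an episode is expected to contain. The section states a floor of two and then calculates as if two were the average. The episode length and CAM interval given just before imply nearly three.

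If episodes hold more readings than assumed, each reading carries less independent information, and a fixed count of 170 buys less precision than stated. Anyone who judges the study by whether it reached 170 CAM-positive readings would believe that the ±5-point goal had been met when it had not. Sensitivity is the quantity on which the whole sample size rests, so the stated requirement should follow from the stated inputs.

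**Working it through.** **Inputs** (Sample size calculation unless noted): sensitivity p = 0.92; 95% confidence, z = 1.96; intraclass correlation 0.5; mean episode 11 days; CAM interval 4 days, or 3.5 days on average if twice weekly (Study assessments); incidence 21.8% in 24 weeks; 258 residents for 36 weeks.

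**Step 1: reproduce the plan.**

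- Unadjusted number: z²p(1−p)/d² with d = 0.05 gives 1.96² × 0.0736 / 0.0025 = 113.1, so 113. The precision statement therefore means ±5 percentage points absolute. A relative 5% would give 133.6.
- Design effect: 1 + (m − 1) × 0.5 equals 1.5 only when m = 2. Then 113 × 1.5 = 169.5, so 170.
- Residents: 170/2 = 85 episodes. Incidence scaled linearly to 36 weeks is 0.218 × 36/24 = 0.327. Then 85/0.327 = 259.9, or 85/0.33 = 257.6 if the rate is rounded, so 258. This route uses m = 2 again and assumes no loss.

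**Step 2: use the plan's own episode length and interval.** Here m is 11/4 = 2.75, or 11/3.5 = 3.14. The number required is 113 × design effect. The half-width from 170 readings is 1.96 × √(0.0736 × design effect / 170).

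| Readings per episode (m) | Design effect | Readings required | Episodes required | Half-width from 170 readings |
|---|---|---|---|---|
| 2 (as used) | 1.5 | 170 | 85 | 5.0 points |
| 2.75 (4-day interval) | 1.875 | 212 | 212/2.75 = 77 | 5.6 points |
| 3.14 (twice weekly) | 2.07 | 234 | 234/3.14 = 75 | 5.9 points |

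At m = 2.75, 170 readings are worth 170/1.875 = 90.7 independent ones; at 3.14 they are worth 82.1. Both fall short of 113.

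**Step 3: check what 258 residents deliver.** With no loss, 258 × 0.327 = 84.4 episodes.

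| m | Readings from 258 residents | Effective readings | Half-width | Residents needed for ±5 |
|---|---|---|---|---|
| 2 | 168.7 | 112.5 | 5.0 points | 259.4 |
| 2.75 | 232 | 123.7 | 4.8 points | 235.8 |
| 3.14 | 265 | 128.0 | 4.7 points | 227.9 |

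The margin in residents is 1 − 235.8/258 = 8.6% at m = 2.75 and 1 − 227.9/258 = 11.7% at m = 3.14. It exists because effective readings per episode, m divided by the design effect, rise from 2/1.5 = 1.33 to 2.75/1.875 = 1.47 and 3.14/2.07 = 1.52.

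**Step 4: sensitivity to how incidence is scaled.** If 21.8% is treated as a risk and extended to 36 weeks as 1 − 0.782^1.5 = 30.8%, 258 residents give 79.6 episodes. At m = 2.75 that is 218.9 readings and ±4.9 points. The goal is still met, with a margin of about 3%.

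**The case against.** The strongest defence is that the plan is consistent within itself. It uses m = 2 in both steps, all three of its figures reproduce, and for the number of residents two is the cautious choice. A low m might also stand in for CAMs not done, or for CAMs that turn out negative within a fluctuating episode. The first part stands: 258 residents are adequate at any m from 2 to 3.14 if nobody is lost. The second is a possible motive that the text does not give. The text presents two as a minimum, and being cautious about residents does not make 170 the right number of readings.

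A second defence is that nothing is lost in practice, and it limits the consequence. The Study assessments section fixes nine months of assessment, and no section ends the study at 170 readings. A reader might infer that the study would stop there and miss its precision, but the documents do not say so. At 2.75 readings per episode the same residents would be expected to supply about 232.

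A reader might also infer that deaths, withdrawals and missed DOSS forms make the shortfall worse. These affect whether a target is reached, not the precision that 170 readings give. The article states no loss rate, and it is a condensed account whose full protocol may hold an allowance. Missing DOSS is a feasibility outcome, studied by "examining patterns and rates of missing data on care home staff completed DOSS assessments", but a missed daily form need not lose a pair, since the nearest DOSS is used. A given rate of missing forms therefore cannot be read as the same rate of lost pairs.

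Finally, 3.14 replaces the section's own 4-day interval with the average spacing of a twice-weekly schedule. It is shown here as an upper figure; the main result rests on 2.75.

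**Conclusion.** The concern holds for the reading target only. On the plan's own inputs, ±5 points needs about 212 CAM-positive readings (234 at twice-weekly spacing), which is 25% (38%) more than 170. Taken alone, 170 readings give ±5.6 (5.9) points, a loss of 0.6 to 0.9 points of half-width. This is a modest error in a stated figure, and correcting it costs almost nothing.

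It does not follow that the study is too small. With no loss, 258 residents give ±4.8 (4.7) points, with about 9% (12%) of residents in reserve, or about 3% at m = 2.75 if incidence is extended as a risk.

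The result assumes an intraclass correlation of 0.5, a sensitivity of 92%, and that every scheduled CAM within an episode is done and positive. If some are not, m falls towards two: at m = 2.5 the requirement is 198 readings, and 170 would give ±5.4 points.

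**What to change.** In the Sample size calculation section:

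1. State one expected number of readings per episode (2.75 on the section's figures, 3.14 if the twice-weekly schedule is meant) and use it both for the design effect and for the yield from residents.
2. Replace 170 with about 212 (up to 234) CAM-positive readings that have a paired DOSS, and give the matching number of episodes, about 77. The 85 episodes behind the present figure belong to the two-per-episode calculation and should not be carried over.
3. State the precision expected from 258 residents: about ±4.8 points at 2.75 readings per episode, with no loss.
4. Say that the precision goal is ±5 percentage points absolute.

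The cost is a rewording and a larger stated reading target. No additional residents or assessments are needed.

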### Data analysis plan

We aim to evaluate the feasibility of embedding the existing DOSS instrument into routine care rather than to evaluate the content of the questionnaire. Feasibility of administration of the DOSS by care home staff will therefore be examined through exploring the rates of missing data, and by examining the intraclass correlation coefficients between staff-administered DOSS assessments.

A receiver operating curve will be plotted to determine the optimal cut-point for the 25-item DOSS. Sensitivity, specificity, positive and negative predictive values, likelihood ratios positive and negative, and a diagnostic OR will be calculated with 95% confidence limits.

Correlation of the 25-item DOSS with the CAM severity score will be used to determine whether the DOSS may be used as a marker of delirium severity.

Item response theory (non-parametric and parametric if appropriate) will be performed to determine the scaling properties of the 25-item DOSS and to identify whether there are any redundant items to form a care home-specific version of the DOSS.

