For an instrument to have utility for delirium detection in routine care in the care home setting, it should be brief and not require specialist knowledge or training to administer. It should have high sensitivity (a low false-negative rate), and acceptable specificity (a high true-negative rate).

Fourteen reviews of delirium assessment instruments have identified six externally validated instruments that may be administered by nursing staff. Of these, two may have utility as screening tools for delirium in the care home environment. These are the Delirium Observation Screening Scale (DOSS)^7^ and the Nursing Delirium Screening Scale (NuDESC).^8^ Sensitivity of the DOSS is comparable with the NuDESC for detection of delirium (pooled sensitivity for the DOSS is 92% (95% CIs 74% to 98% 2 studies, 178 participants) vs 96% for the NuDESC (95% CI 80% to 100% 1 study, 100 participants)).^9^ However, the specificity of the DOSS is higher (82% (95% CI 66% to 92%) vs 69% (95% CI 59% to 79%)); therefore, the DOSS was chosen as the candidate instrument for the study. The DOSS comprises items which seek objective assessment of the behavioural aspects of the DSM-IV delirium diagnostic criteria: onset of a short period of altered consciousness; reduced ability to focus, sustain or shift attention; a change in cognition (memory deficit, disorientation, language disturbance); and perceptual disturbance not better accounted for by a pre-existing, established or evolving dementia. The DSM also stipulates that, for a diagnosis of delirium, there is evidence from the clinical assessment that these changes are associated with a general medical condition and that there is fluctuation during the course of the day.

The psychometric properties of the DOSS have been assessed in acute and rehabilitation settings,^7^
^10^ but the utility of the DOSS in care homes has not been evaluated. This study aims to determine how the DOSS performs as a screening instrument for delirium when administered by care home staff in comparison to a research standard assessment based on the Confusion Assessment Method (CAM).^11^

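### The DOSS cut-point is chosen on the study's own ROC curve and its accuracy reported from the same cohort, under an unstated criterion: modest optimism, and no tie to the sensitivity the study is sized for

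*Protocol article*

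**What the plan says.** In the protocol article, the Data analysis plan section sets the threshold in one sentence: "A receiver operating curve will be plotted to determine the optimal cut-point for the 25-item DOSS". The next sentence gives the output: "Sensitivity, specificity, positive and negative predictive values, likelihood ratios positive and negative, and a diagnostic OR will be calculated with 95% confidence limits". The natural reading is that these measures are calculated at the chosen cut, in the same residents. The article describes one cohort in up to four homes. It mentions no threshold fixed beforehand, no separate validation sample and no correction for selection, and it does not say what makes a cut-point optimal.

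Two other sections bear on this.

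- The Introduction says of a usable instrument: "It should have high sensitivity (a low false-negative rate), and acceptable specificity (a high true-negative rate".
- The Sample size calculation section works from a known sensitivity: "Using the pooled estimate for sensitivity (92%) of the DOSS from previous studies". It concludes that "there would need to be 113 measurements of CAM positive delirium during the study period", raised to 170 by a factor of 1.5 for repeated measures.

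The DOSS assessments section says that some items were reworded and that each of the 25 items is scored 0 or 1. The total therefore runs from 0 to 25. The article gives no earlier cut-point for this version.

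**The concern.** Two things follow from the plan as written.

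1. **Optimism.** The cut that looks best in a sample looks best partly by chance. Its apparent sensitivity in that sample exceeds, on average, what the same cut would achieve in new residents.
2. **An open criterion.** Without a rule, the choice can be made after the curve is seen, and it need not respect the emphasis on sensitivity in the Introduction. If the chosen cut has sensitivity well below 92%, the precision calculation no longer describes the estimate that will be reported.

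The Ethics and dissemination section sends results to commissioning groups, general practitioners and care homes. They are likely to read a reported cut-point and its sensitivity as ready for use.

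**Working it through.** **Step 1: reproduce the plan's figure.** Inputs from the Sample size calculation section: p = 0.92, 95% confidence, design factor 1.5. The precision is worded as "with 95% confidence that the observed value is within 95% of the true value"; the stated number matches ±5 percentage points.

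- n = 1.96² × p(1 − p) / d² = 3.8415 × 0.92 × 0.08 / 0.05² = 113.09, so 113 as stated.
- 113 × 1.5 = 169.5, so 170 as stated.
- A literal 5% relative margin (d = 0.05 × 0.92 = 0.046) would give 134, so ±5 points is what was used.
- Accrual: 258 × 0.218 × 36/24 = 84.4 episodes; × 2 readings = 168.7, consistent with 170.

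The calculation takes 92% as the sensitivity at the operating cut and makes no allowance for selecting that cut.

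**Step 2: where an equal-weight optimum could fall.** Take the article's planning pair, sensitivity 0.92 and specificity 0.82, and assume normal scores with equal variance.

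- Separation = z(0.92) + z(0.82) = 1.405 + 0.915 = 2.320.
- The maximum Youden index lies at the midpoint: sensitivity = specificity = Φ(2.320 / 2) = Φ(1.160) = 0.877.

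On a rounded 0 to 25 score, the best cut had sensitivity 0.876 and specificity 0.878. With unequal variances calibrated to the same pair it had 0.849 and 0.960. So even where a 92%/82% cut exists, an equal-weight rule lands at about 0.85 to 0.88.

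**Step 3: effect on the planned precision.** Same formula, d = 0.05:

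- p = 0.88: 3.8415 × 0.1056 / 0.0025 = 162.3; × 1.5 = 243.4.
- p = 0.85: 3.8415 × 0.1275 / 0.0025 = 195.9; × 1.5 = 293.9.
- With 113 effective positives and p = 0.85, the half-width is 1.96 × √(0.1275 / 113) = 0.066, or ±6.6 points instead of ±5.

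**Step 4: size of the optimism.** Simulation with 20,000 replicates per scenario: choose the cut on the sample ROC, then subtract the true sensitivity at that cut from the apparent one. Assumptions not in the article: rounded-normal scores (the two sets in step 2, plus a weaker set with AUC about 0.85), 1,000 to 5,000 effective CAM-negative readings, and two readings of *optimal*. Effective positives of 113 correspond to 170 / 1.5; 57 would correspond to a design factor of 3 (170 / 3 = 56.7); 40 is a pessimistic case.

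| Effective positives | Maximum Youden index | Highest cut with observed sensitivity ≥ 90% |
|---|---|---|
| 170 | +0.5 to +1.0 points | +0.4 |
| 113 | +0.8 to +1.5 | +0.6 to +0.7 |
| 57 | +1.4 to +2.5 | +1.2 to +1.4 |
| 40 | +2.1 to +3.3 | +1.8 to +1.9 |

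The sign was positive in every scenario. Specificity hardly moved, because CAM-negative readings are plentiful: in the Youden runs at 40 and 57 positives it was overstated by 0.07 to 0.14 points. In the scenarios calibrated to 92%/82%, with 113 effective positives, the Youden cut had true sensitivity below 0.90 in 88% to 100% of simulated studies.

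**The case against.** Much of the other side stands.

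- **The bias is small.** At the planned size, 0.4 to 1.5 points sits well inside a planned ±5. This stands and limits the severity.
- **A cut-point has to be derived.** The items are reworded, scoring is 0/1, and no earlier threshold is given. This also stands. The fault is reporting accuracy at that cut uncorrected, not deriving it.
- **The article names no criterion.** A reader might infer that it adopts a symmetric optimum and so contradicts its Introduction. It does not: neither Youden nor equal weighting appears, and *optimal* can be read in line with the screening purpose. The Introduction also glosses acceptable specificity as a high true-negative rate, and it prefers the DOSS to an instrument of comparable sensitivity because "the specificity of the DOSS is higher (82% (95% CI 66% to 92%) vs 69% (95% CI 59% to 79"%). Step 2 shows what the wording permits, not what it states.
- **92% is not a performance target.** A reader might infer that the cut must reach it. It is a pooled planning value with a 95% CI of 74% to 98%, from other settings. A high floor also has a price. If every planned reading were made, 258 × 72 = 18,576 (two per week for 36 weeks), of which 18,406 would be negative. At 92%/82% that gives 0.18 × 18,406 = 3,313 false positives against 0.92 × 170 = 156 true positives, a predictive value of 4.5%. The trade-off belongs to the investigators.
- **Intervals.** A reader might infer that selection alone ruins the 95% limits. In the step 4 simulation, with independent readings, coverage stayed near 95%. Ignoring a design factor of 1.5 gives 2Φ(1.96 / √1.5) − 1 = 89.0% with no selection at all, so a marked shortfall would mainly reflect clustering.
- **Shortened scale.** The plan will "identify whether there are any redundant items to form a care home-specific version of the DOSS". A reader might infer a second layer of optimism. But items are to be dropped by item response theory, not by maximising accuracy against the CAM, and no accuracy estimate for a short form is promised.
- **Detail left to a fuller document.** An analysis plan not shown may define the criterion or a correction. That is possible, but the article itself commits to choosing the cut on the study curve, and a correction is a better method than the one described.

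**Conclusion.** The concern holds in a limited form. Followed as written, the plan yields accuracy figures that are modestly optimistic, almost entirely in sensitivity: about 0.4 to 1.5 points at 113 to 170 effective positives, and up to about 3 points at about 40. Measures built on sensitivity inherit this. The unstated criterion matters more. An equal-weight choice, permitted but not stated, could give sensitivity of about 0.85 to 0.88, at which ±5 points would need roughly 243 to 294 CAM-positive readings instead of 170.

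These sizes rest on assumed score distributions and on the article's 92%/82% carrying over to care homes. The direction of the bias did not depend on those choices in any scenario tried. Severity is moderate: it should be fixed, it is a cheap improvement, and it does not threaten the validity of the study.

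**What to change.** Before the analysis:

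1. State a cut-point rule consistent with the Introduction, for example the best specificity among cuts that meet a minimum sensitivity set by the investigators.
2. Repeat the whole cut-point selection within a bootstrap that resamples residents. Report optimism-corrected accuracy with intervals that allow for repeated readings in the same resident.
3. Label uncorrected figures as apparent.
4. Apply the same procedure to a shortened DOSS only if its accuracy is reported.

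The cost is a few sentences in the plan and a little more analysis, with no new data. The downside is slightly lower and wider headline figures. The rule needs to be fixed before the ROC curve is seen, since one stated afterwards would carry little weight.
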